#### Analyses

We will apply qualitative and quantitative methods to identify factors affecting trial feasibility. Further, we will assess the feasibility of the intervention and provide knowledge that can be used to explore indications of an inherently faulty concept or theory or implementation failure; see, for example, the work by [name] and [name] [37].

We will apply a thematic analytical strategy to both interviews and observations, using themes such as, for example, ‘randomisation experiences’, ‘relationship between families and professional helpers’, ‘organisational boosters and barriers to implementation’ and ‘contribution of the intervention to existing services’.

Retention to the trial will be analysed by investigating the response rates. At each timepoint for survey data, we will calculate the pooled response rate and use a chi-squared test to check whether response rates differ by study arm.

To assess adherence to the trial, we will calculate the rate of families who withdrew their consent within 12 months of recruitment and use a chi-squared test to check whether adherence to the trial differs by study arm. To assess adherence to the intervention, we will calculate the rate of families who terminate the intervention within the first 3 months after enrolment.

The secondary outcomes will be analysed according to conventional procedures for RCTs. Using survey data and administrative data from the municipal CWS, we will examine records of child maltreatment, child behaviour, parenting behaviour, parental stress, parent locus of control, family routines, parental mental health, self-efficacy, social support, relations to professional helper, relations to partner and service use. All analyses and results will be conducted and presented according to recognised academic standards [38], including adherence to the intention-to-treat principle, where all consenting participants are included in the analyses. For binary outcomes, we will apply logistical models and report effect sizes as odds ratios. For continuous outcomes, we will use linear models and report coefficients as standardised effect sizes (Cohen’s *d*). The analyses will be adjusted for observed differences at baseline and repeated hypothesis tests.

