#### Sample size

The study aim to include 90 families, 30 from each of the sites. This number is expected to be sufficient to inspect randomisation routines, acceptability, retention and adherence. Contrary to a potential full-scale RCT, the pilot study does not aim to estimate effect sizes. However, if the retention is 80%, and we apply conventional power calculation assumptions (*α* = 0.05 and power set to 80%), our sample (*N* = 90) would be sufficient to detect a medium-to-large effect (*d* = 0.67) on continuous outcomes.

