## Discussion

This feasibility study allow us to investigate the acceptability of the Family Partner intervention for staff and families and evaluate the feasibility of a full-scale RCT of the intervention. If rates of recruitment, retention and response are adequate, and the study procedures are found to be acceptable, we will consider conducting a full trial. As this is a pilot feasibility trial, it is not powered to estimate the effects of the intervention. In addition, there are further limitations associated with treatment contrast in this study, that is, the comparison between the Family Partner intervention and the control group.

The organisation of municipal services in Norway, specifically CWS, varies across different locations, resulting in varying access to resources and services. Consequently, CWS is also organised differently across municipalities, resulting in differing service offerings. Furthermore, there is limited practical integration between specialist health services, such as district psychiatric centres, municipal mental health services and CWS. This lack of collaboration makes it difficult to predict the services the control group would receive. Additionally, there are considerable differences in the educational backgrounds of child welfare workers in various geographic locations, which could potentially create disparities in the results when comparing different sites. Hence, the research group will have to carefully assess the services provided to the control group.

Results from the pilot will help to assess the acceptability of the intervention’s implementation and delivery among frontline practitioners in the CWS. This information will be crucial to understand whether the intervention is a suitable fit for the Norwegian child welfare infrastructure and local services.

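### Covariates for the secondary-outcome models are to follow the baseline differences that happen to be observed, when they should be named in advance

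*Protocol article*

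**What the plan says.** The Analyses section sets out the secondary-outcome models in three statements. For continuous outcomes: "For continuous outcomes, we will use linear models and report coefficients as standardised effect sizes" (Cohen's d). For binary outcomes: "For binary outcomes, we will apply logistical models and report effect sizes as odds ratios". For covariates and multiplicity together: "The analyses will be adjusted for observed differences at baseline and repeated hypothesis tests".

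The article names no covariate and does not define what counts as a difference. The Randomisation section describes a coin-toss function in the survey that gives each family a 50% chance of either arm, and mentions no stratification. In Table I, the measures marked at baseline are parental stress, family routines, self-efficacy, working alliance and the parent's own childhood. The first four of these are also outcomes; the fifth is background only. The Discussion says that child welfare workers' education differs between locations, "which could potentially create disparities in the results when comparing different sites".

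The Secondary outcomes section says that these results can feed a sample size calculation for a full trial.

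**The concern.** After a coin-toss allocation, differences between the randomised arms at baseline arise by chance. A rule that adjusts for the differences seen has two effects.

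- The fitted model depends on the data, so the standard error and p-value no longer have exactly their stated properties.
- The covariate most likely to predict the outcome, its own baseline score, enters only when it looks imbalanced. Whenever it looks balanced, its precision is given up although it has been collected.

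This is a rule that the article states, not a detail left to a fuller plan. A later plan that fixed covariates regardless of balance would depart from the sentence as it stands. At stake is the quality of the secondary estimates, which are to be reported as standardised effects and odds ratios and may be carried into the design of a full trial.

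**Working it through.** **Inputs from the article (Sample size).** "The study aim to include 90 families, 30 from each of the sites"; retention 80%; α = 0.05; power 80%; detectable d = 0.67. Analysed: 90 × 0.80 = 72, or 36 per arm.

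**Assumptions (not in the article).** Two-sided test; equal arms of 36; one normal baseline covariate; baseline-outcome correlation r from 0.3 to 0.7; a difference counts as observed if a baseline t-test gives p<0.05, with p<0.20 as a variant.

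**Step 1: the plan's own figure.** By normal approximation, detectable d = (1.960 + 0.842) × √(2/36) = 2.802 × 0.2357 = 0.660. By the noncentral t it is 0.670, and power at d = 0.67 is 80.05%. The stated 0.67 is reproduced, and it is the figure for an unadjusted comparison.

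**Step 2: always adjusting for the baseline value.** The residual SD falls by the factor √(1 − r²), so detectable d = 0.660 × √(1 − r²):

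- r = 0.3: 0.660 × 0.954 = 0.63
- r = 0.5: 0.660 × 0.866 = 0.57
- r = 0.6: 0.660 × 0.800 = 0.53
- r = 0.7: 0.660 × 0.714 = 0.47

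**Step 3: simulation of the imbalance-triggered rule.** 40,000 trials per setting, 36 per arm, p<0.05 trigger:

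| r | Type I error, triggered | Power at d = 0.67, triggered | Power at d = 0.67, always adjusted |
|---|---|---|---|
| 0.3 | 4.7% | 80% | 83% |
| 0.5 | 4.5% | 81% | 90% |
| 0.6 | 4.0% | 82% | 94% |
| 0.7 | 3.6% | 82% | 97% |

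The always-adjusted analysis keeps type I error at 5.0-5.1%.

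**Step 4: a larger run and a looser trigger.** With 200,000 trials per setting, the p<0.05 trigger gives type I error of 4.7%, 4.3% and 3.7% at r = 0.3, 0.5 and 0.7. The p<0.20 trigger gives 4.6%, 3.8% and 2.6%, with power of 81%, 83% and 86%. Always adjusting again gives 4.9-5.1%, with power of 83%, 90% and 97%.

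**Why the error is conservative.** When the trigger is not met, the unadjusted standard error of about 0.236 (√(2/36)) is used. Large baseline imbalances have by then been screened out, so the estimates vary less than that standard error claims. At r = 0.5 the SD of the effect estimate is 0.235 unadjusted, 0.228 with the p<0.05 trigger, and 0.205 when always adjusted.

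**Step 5: reach.** The Analyses section lists twelve secondary outcomes, and Table I gives a baseline value for four of them. Steps 2 to 4 apply to those four. For the other eight, and for any gain from a site term, nothing has been calculated.

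**The case against.** **The trigger is not in the article.** No baseline test is planned; the chi-squared tests concern response rates and consent withdrawal. The sentence could also mean adjusting for measured baseline differences whatever their size, which for a baseline score is close to always adjusting. This stands as a limit on the numbers: they describe one plausible form of the rule. It does not remove the point, because the natural reading ties the covariates to the imbalance seen.

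**A reader might infer an inflated error rate.** The article does not support that. Under a fixed trigger the error is below 5%. If an analyst reported the more favourable of the adjusted and unadjusted results, simulation gives 6.4% (r = 0.3) to 8.4% (r = 0.7), but the article plans no such procedure. With no trigger stated, discretion over covariates could move the error upward. That is a risk and not the size of the stated rule.

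**A reader might apply the power gain to every outcome.** It covers only four of the twelve.

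**The correlation may be low.** Parental stress is next measured at 12 and 18 months. Baseline working alliance is recorded before randomisation, so intervention families may then be rating a different helper from the later family partner (an inference). At r = 0.3 the gain is only about 3 percentage points. This stands.

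**The site evidence is thin.** The Discussion remark concerns comparisons between sites, and no stratification by site is described. Site is a sensible covariate to prespecify, but the article does not show that omitting it biases the comparison of arms.

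**The stakes are limited.** The Sample size section says that the pilot does not aim to estimate effect sizes, and no success criterion uses an adjusted secondary analysis. This stands, and it lowers the severity.

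**Conclusion.** The point holds as a flaw in a stated rule, of minor to moderate severity. Letting observed imbalance choose the covariates makes the tests somewhat conservative and gives up precision that the collected data could provide.

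For the four outcomes with a baseline value, the power given up at d = 0.67 under the p<0.05 trigger is about 3 points at r = 0.3 (83 − 80), 9 at 0.5 (90 − 81), 12 at 0.6 (94 − 82) and 15 at 0.7 (97 − 82). The trigger and r are both assumed. The loss is negligible at the low end and material from r = 0.5 upward. Confidence is high that the wording is a poor rule and lower for the magnitude.

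The pilot's primary outcomes and its success criteria are untouched. The practical consequence is confined to the secondary estimates and to any full-trial sample size calculation that draws on them.

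**What to change.** Replace the covariate part of the sentence with:

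> Each model adjusts for site and, where collected, the baseline value of the same outcome, regardless of observed balance; baseline differences are not used to select covariates.

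Keep the commitment to adjust for repeated hypothesis tests as a separate sentence. Make clear that the baseline value is meant for the four outcomes that Table I marks at baseline. The questionnaire was shortened after the first families were recruited, so any wider baseline data from those families would not serve as a covariate for the whole sample.

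The cost is one sentence, settled before the outcome data are analysed. Site and the four baseline scores are already collected, so no new data, families or procedures are needed.

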#### Success criteria

We will consider the pilot trial a success if we achieve the following goals:

(1) 70% of the participants complete their allocated treatment (at least 9 months) and this is equal in both groups (*p* > 0.05);(2) response rates are above 70% and are equal in both groups (*p* > 0.05);(3) all sites are able to recruit the necessary staff, retain at least 50% of family partners for at least 18 months, and are able to recruit new staff in the event of turnover.

If the trial is successful, we will report estimated costs for an upscaled trial.

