### Family Partner intervention

The Family Partner intervention is an intensive home-visitation family intervention that aims to reduce child maltreatment among at-risk parents by improving parental skills, agency and trust in the welfare services, and children’s well-being. The intervention is being delivered by child welfare workers employed by the Norwegian CWS. These workers typically hold a 3-year bachelor’s degree in social work or an equivalent qualification. During the study, the child welfare workers receive implementation support, such as training and supervision in the Family Partner methodology.

The Family Partner intervention procedures include: (a) parental training; (b) home visitations; (c) practical assistance; (d) a measurement feedback system including monthly well-being scoring schemes; (e) an emphasis on a therapeutic relationship with parents to create trust; and (f) coordination of services. Central to the intervention is the family partner, who is a professional employed to ensure that the families receive close, empowering and structured support.

The intervention is based on three theoretical perspectives: Banduras’s [24] theory of self-efficacy, which states that your belief in your abilities impacts your chance of succeeding; Bronfenbrenner’s [25] ecological theory of the family as a context for human development; and Ablon’s [26] theory of the potential of a collaborative problem-solving approach.

The estimated duration of the intervention is 9 months, but it can be extended by 3 months if considered beneficial to the families. The intervention period is divided into three phases: a 3-month start-up phase, a 3–6-month working phase and a 3-month ending phase. During the intervention period, the family partners provide each family with an average of 5 hours of weekly service, with more frequent service at the beginning and less frequent during the ending phase. In total, the number of sessions with each family across the three periods should be between 50 and 100. It should be noted the intervention may be modified based on findings from the pilot study, including assessments provided by the managers of the municipal agencies, family partners, parents and children.

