## Design and methods

### Trial design

The study is a prospective, parallel, pilot randomised trial of the Family Partner intervention. Families in the treatment group receive the Family Partner intervention, while families in the control group receive ordinary child welfare services (e.g., guidance and advice for the family, parent groups or home-based assistance).

After consenting to take part in the study, one of the primary caregivers completes the baseline assessment questionnaire and is then randomised 1:1 to the treatment and control groups.

The recruitment and randomisation of families is an ongoing process. Each family partner can serve up to five families at a time, and each family participate for up to 12 months. When a family leaves the intervention, a new family is recruited and randomised.

The trial is piloted at three sites; two of which are in medium-sized cities and one in a sparsely populated municipality. These sites were included in the pilot based on their motivation for participation, and because they vary in size and location. A flow diagram of the study design is provided in Figure 1.

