We assess retention in the trial by monitoring response rates, that is, whether participants respond to the surveys. We assess adherence to the trial by registering whether families withdraw their consent within 12 months of recruitment. We measure adherence to the intervention by monitoring if, when and why families terminate the intervention.

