**Primary objectives**								
Participant acceptability	Qualitative interviews with participating families, the family partners, and representatives of the Child Welfare Service (CWS) in each municipality							
Retention in the study	Comparison of response rates, that is, how many participants respond to the surveys, by study arm							
Adherence	Monitoring the share of families who terminate the intervention within 3 months of enrolment							

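### Success criterion 1 (9-month completion, equal in both groups) does not match the planned 3-month adherence analysis, and the article states no completion event for control families

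*Protocol article*

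**What the plan says.** All references are to the protocol article.

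- **Success criteria, item 1:** "70% of the participants complete their allocated treatment (at least 9 months) and this is equal in both groups", judged by p > 0.05.
- **Analyses, adherence to the intervention:** "we will calculate the rate of families who terminate the intervention within the first 3 months after enrolment". No comparison by arm is stated for this rate.
- **Table I, Primary objectives, row Adherence:** "Monitoring the share of families who terminate the intervention within 3 months of enrolment".
- **Primary outcomes:** "We measure adherence to the intervention by monitoring if, when and why families terminate the intervention". No 3-month limit is set here.
- **Analyses, adherence to the trial:** "we will calculate the rate of families who withdrew their consent within 12 months of recruitment", with a chi-squared test by study arm.
- **Family Partner intervention:** "The estimated duration of the intervention is 9 months, but it can be extended by 3 months". The phases are a 3-month start-up, a working phase of 3 to 6 months and a 3-month ending.
- **Trial design:** "families in the control group receive ordinary child welfare services (e.g., guidance and advice for the family, parent groups or home-based assistance"). No length of course or end point is given for these services.
- **Discussion:** "This lack of collaboration makes it difficult to predict the services the control group would receive". The same paragraph ends by saying that the research group will have to assess those services carefully.

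**The concern.** Adherence is one of three primary outcomes, and this is the first of three conditions for calling the pilot a success. The criterion needs the proportion completing at least 9 months of allocated treatment, in each arm, and a test between the arms. The planned analysis gives early termination, in one arm, with no test.

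Two things are at stake. First, the reported figure would not answer the criterion. Whoever judges success would have to choose a definition of completion after seeing the data. Second, the 9 months is the length of Family Partner itself. Applied to ordinary services, it would count a service that ended as intended before 9 months as non-completion. The criterion could then fail for a reason unrelated to whether families stay in Family Partner.

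**Working it through.** **The plan's own figure.** The article gives no calculation behind the 70% threshold, so there is none to reproduce.

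**Step 1: the two definitions side by side.**

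| | Success criterion 1 | Analyses and Table I |
|---|---|---|
| Event | Completes allocated treatment | Terminates the intervention |
| Horizon | At least 9 months | 3 months |
| Families | Both arms | Family Partner families only |
| Arm comparison | Yes, p > 0.05 | None stated |

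The 3-month horizon coincides with the start-up phase. Terminations in the working and ending phases do not enter the planned rate.

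**Step 2: what a 3-month rate says about 9 months.** Let q be the share terminated by 3 months. Without further assumptions, 9-month completion is at most 1 − q and could be anything below that. A rate of q above 30% would show that the intervention arm misses 70%, but no value of q above zero shows that it meets 70%.

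To go further, a pattern of termination must be assumed. With a constant hazard, 9-month completion = (1 − q)³:

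| Terminated by 3 months (assumed) | Completing 9 months |
|---|---|
| 5% | 0.95³ = 86% |
| 10% | 0.90³ = 73% |
| 15% | 0.85³ = 61% |
| 20% | 0.80³ = 51% |

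The 70% threshold falls at q = 1 − 0.70^(1/3) = 11.2%. In monthly terms, assumed termination of 2%, 3% or 4% per month gives 0.98⁹ = 83%, 0.97⁹ = 76% or 0.96⁹ = 69%. The corresponding 3-month rates are 5.9%, 8.7% and 11.5%. The verdict on the criterion therefore changes over a narrow range of 3-month rates, and the crossing point depends on the assumed pattern.

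**Step 3: the control arm.** Inputs are 90 families allocated 1:1, so about 45 per arm. The test for criterion 1 is not named. I assume chi-squared without continuity correction, since the Analyses section uses chi-squared for its other arm comparisons.

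Suppose 36 of 45 Family Partner families (80%) complete 9 months.

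- If the 70% is read as pooled, it needs 0.70 × 90 = 63 completers, so 63 − 36 = 27 control families (60%) must have services lasting 9 months.
- With 27 of 45 the test gives p = 0.038, so the equality part fails. With 28 of 45 it gives p = 0.063, and both parts pass.
- With 22 of 45 (49%) the pooled rate is 58/90 = 64% and p = 0.002, so both parts fail although the intervention arm reached 80%.

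These counts are hypothetical. They show only that the result would depend on how long ordinary services happen to last.

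**Step 4: precision if the criterion is judged in the intervention arm.** The half-width of the 95% interval is 1.96 × √(0.70 × 0.30 / 45) = 0.134, or about ±13 points.

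**The case against.** A reader might infer that criterion 1 cannot be evaluated at all. The article does not support that. The Primary outcomes section records whether, when and why families terminate the intervention, with no 3-month cut-off. Nine-month completion in the Family Partner arm can therefore be computed from planned data, even though the Analyses section does not plan it. This objection stands and limits the point.

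A reader might also infer that no adherence analysis goes beyond 3 months or compares the arms. That is not so: consent withdrawal within 12 months is compared by arm. But the article calls this adherence to the trial, and a family can stop a service without withdrawing consent. It does not answer criterion 1 as worded.

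On the control arm, the remark about unpredictable services concerns which services families receive, not whether their duration can be observed. The article also names administrative data on child welfare assistance measures, which could supply start and end dates. A fuller protocol or analysis plan, not shown, may define control-arm completion. That is fair, and it lowers confidence on this half of the point. The article does not link those data to the criterion, however, and no such definition would remove the conflict between 3 and 9 months printed in the article.

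Finally, the article ties no automatic stop to this criterion. It says when the pilot will be considered a success, and that a full trial would then be considered. The numerical examples show that a misleading result is possible, not that it is likely.

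**Conclusion.** The point holds as a mismatch within the article. Criterion 1 asks for 9-month completion in both arms with a comparison. The planned analysis of adherence to the intervention gives 3-month termination in Family Partner families only. For controls, the article states no completion event and no service duration, so the equality part is not defined as written.

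The size depends on an assumed termination pattern. Under a constant hazard, 3-month termination of 5% to 20% corresponds to 9-month completion of about 86% to 51%, crossing 70% at about 11%. The mismatch between the sections needs no such assumption and is certain. The control-arm part is less certain, because a document not shown may supply the definition. The finding does not extend to saying that the intervention-arm completion rate is unobtainable, or that the pilot will fail.

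**What to change.** Reconcile Primary outcomes, Table I, Analyses and Success criteria, and record the definition before results are judged:

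1. Judge the 70% threshold on the proportion of families allocated to Family Partner who are still in the intervention at 9 months, with a 95% confidence interval, using the termination dates already monitored.
2. Keep the 3-month termination rate in Analyses and Table I as a descriptive early-dropout figure.
3. Base the between-arm comparison on consent withdrawal within 12 months, already planned in both arms. If a comparison of treatment completion is still wanted, define the control-arm completion event in advance, for example from child welfare administrative records of assistance measures.

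Items 1 and 2, and the consent-withdrawal comparison, need changes of wording and no new data. A control-arm completion event would need the administrative records to be linked to this purpose. The price of item 1 is precision: the completion rate rests on about 45 families rather than 90, about ±13 points at 70%, so an observed rate near the threshold will not settle on which side the true rate lies.

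### Success criteria 1 and 2 take a non-significant test (p > 0.05) as showing that the arms are equal, which about 45 families per arm cannot show

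*Protocol article*

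**What the plan says.** The Success criteria section lists three goals. The first is that "70% of the participants complete their allocated treatment (at least 9 months) and this is equal in both groups (*p* > 0.05"). The second is that "response rates are above 70% and are equal in both groups (*p* > 0.05"). The third concerns staffing ("all sites are able to recruit the necessary staff, retain at least 50% of family partners for at least 18 months") and contains no comparison between arms.

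The Analyses section supplies the test for response. At each survey timepoint, "we will calculate the pooled response rate and use a chi-squared test to check whether response rates differ by study arm". Neither section gives a tolerable difference or a confidence interval for these rates, or says which survey decides criterion 2.

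On size, the Sample size section says "The study aim to include 90 families, 30 from each of the sites", and adds: "This number is expected to be sufficient to inspect randomisation routines, acceptability, retention and adherence". The only calculation there concerns continuous outcomes.

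**The concern.** A p-value above 0.05 says that the data do not rule out equal rates. It does not say that the rates are close. In a small pilot a large true difference will often give such a p-value, so the clause passes partly because the sample is small.

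Retention and adherence are primary outcomes, and criteria 1 and 2 are how they are judged. Most secondary outcomes are reported by parents in the surveys, so unequal response between arms is a direct threat to a full trial. A rule that is insensitive to unequal response could carry the problem forward unnoticed.

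**Working it through.** **Inputs.** From the protocol article: 90 families allocated 1:1, so about 45 per arm (a simple coin toss, so actual arm sizes may differ); chi-squared test; threshold above 70%; equality if p > 0.05. For criterion 1 the Analyses section names no between-arm test of completion, so the same test is assumed. True response rates in each arm, and arm sizes below 45, are assumptions shown as a range.

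**The plan's own figure.** With 80% retention there are 0.8 × 90 = 72 families, 36 per arm. A two-sided t-test at α = 0.05 with 80% power detects d = 0.670, which agrees with the stated 0.67. The figure is correct, but it concerns continuous outcomes and does not support a claim that two rates are equal.

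**Power of the equality clause.** At 45 per arm, 80% power needs a true gap of about 23 points if the higher arm is at 90%, and about 27 if it is at 80%. Power is about 59% for 85% v 65% and about 40% for 85% v 70%; 80% power for those gaps would need 73 and 121 per arm.

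**Largest observed gap that passes at 45 per arm** (no continuity correction), using X² = N(ad − bc)² / (n₁n₂ × responders × non-responders):

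- *70% read as pooled:* 36/45 v 28/45. Pooled rate 64/90 = 71.1%. X² = 90 × (36×17 − 9×28)² / (45×45×64×26) = 3.46, p = 0.063. The difference is 17.8 points with SE √(0.80×0.20/45 + 0.622×0.378/45) = 0.0937, so the 95% CI is −0.6 to 36.1 points. The rule calls this equal.
- *70% read per arm:* 39/45 v 32/45 (86.7% v 71.1%). X² = 90 × (39×13 − 6×32)² / (45×45×71×19) = 3.27, p = 0.07. The difference is 15.6 points.

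With a continuity correction, which the article does not mention either way, the pooled-reading maximum rises to 20.0 points (37/45 v 28/45, p = 0.060).

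**Probability of passing at one survey**, by summing the two binomial distributions over all outcomes that meet the rule:

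| True rates | Clause or rule | 45 per arm | 30 | 20 |
|---|---|---|---|---|
| 85% v 65% | p > 0.05 alone | 38% | 57% | 69% |
| 85% v 65% | pooled > 70% and p > 0.05 | 34% | 45% | 52% |
| 82.5% v 67.5% | pooled > 70% and p > 0.05 | 52% | 58% | 60% |
| 80% v 70% | pooled > 70% and p > 0.05 | 67% | 67% | 65% |
| 80% v 80% | pooled > 70% and p > 0.05 | 93% | 91% | 87% |

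On the per-arm reading, 85% v 65% passes 19% of the time at 45 per arm.

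**The case against.** **The size depends on a reading that the text does not settle.** Criterion 2 can be read as each group exceeding 70%. The pooled rate appears in the Analyses section, which the criterion does not cite. On the per-arm reading the 80% v 62% example fails, and the flaw is capped at 15.6 points and 19%. This stands: a reader might infer that the protocol definitely lets one arm fall below 70%, and the article does not go that far. The logical error is the same on both readings.

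**A reader might infer that the pilot passes more easily the fewer families it recruits.** That holds for the p > 0.05 clause alone. It does not hold for the whole criterion in general: at 80% v 70% the pass probability is flat to slightly falling, and when the arms are truly equal it falls with smaller arms, because the 70% threshold becomes noisier. The Discussion also makes adequate recruitment a condition for considering a full trial, though without a figure.

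**A reader might also infer that repeated testing makes sound pilots fail by chance.** That requires every survey to pass, which the article does not say. The Abstract lists four follow-ups and Table I has five, so the upper limits with independent tests would be 1 − 0.95⁴ = 18.5% or 1 − 0.95⁵ = 22.6%. If all surveys had to pass, the single-survey pass probabilities above would be too high, so the two complaints cannot be combined.

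**The consequences are modest.** Success leads to the reporting of estimated costs, and a full trial is only to be considered. Response is compared by arm at every survey in any case. This stands and limits the severity.

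**Conclusion.** Wrong as written; should be fixed. Criteria 1 and 2 state a decision rule that takes a non-significant test as showing equality, with a sample that reaches 80% power only for gaps of about 23 to 27 points. For criterion 2 at one survey with 45 per arm, the largest observed gap that passes is 17.8 points if 70% is pooled and 15.6 points if it applies per arm. Assumed true rates of 85% v 65% pass 34% or 19% of the time respectively. These figures assume equal arms and no continuity correction.

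This is not a detail left to an analysis plan, because the article prints the rule itself. It is also not fatal to the pilot: no effect estimate depends on it.

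**What to change.** In both criteria 1 and 2, delete the p > 0.05 clause. Require instead that the observed difference between arms is no larger than a prespecified limit that the sponsor justifies, and report it with its 95% CI. Fifteen points is used below only as an example; the article gives no margin. State that the 70% threshold applies to each arm. For criterion 2, name the one survey that decides and give the others descriptively.

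Report the number recruited beside the result, because a rule on the observed gap also loosens in small samples. With at least 70% in each arm and a 15-point limit, true rates of 85% v 65% pass 17%, 24% and 31% of the time at 45, 30 and 20 per arm.

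Formal equivalence is not a realistic demand: with both rates truly 80% and a 15-point margin, two one-sided 5% tests with 80% power need about 122 per arm. At 45 per arm the 95% CI half-width is about 1.96 × √(2 × 0.8 × 0.2 / 45) = 16.5 points, so the interval will be wide and should be shown as such.

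The cost is wording, plus a stricter rule. With a 15-point limit and 45 per arm, against the pooled reading, the pass probability falls from 93% to 86% if both arms are truly at 80%, and from 79% to 60% if both are at 75%. At 85% v 65% it falls from 34% to 17%. Against the per-arm reading that last change is only from 19% to 17%, so much of the gain comes from settling that 70% applies to each arm.
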